# Targeting functional fitness, hearing and health-related quality of life in older adults with hearing loss: Walk, Talk 'n' Listen, study protocol for a pilot randomized controlled trial

**DOI:** 10.1186/s13063-017-1792-z

**Published:** 2017-01-28

**Keywords:** Hearing loss, Disability, Functional fitness, Auditory rehabilitation, Loneliness, Socialization, Older adults

## Abstract

**Background:**

Hearing loss (HL) is a disability associated with poorer health-related quality of life including an increased risk for loneliness, isolation, functional fitness declines, falls, hospitalization and premature mortality. The purpose of this pilot trial is to determine the feasibility and acceptability of a novel intervention to reduce loneliness, improve functional fitness, social connectedness, hearing and health-related quality of life in older adults with HL.

**Methods:**

This 10-week, single-blind, pilot randomized control trial (RCT) will include a convenience sample of ambulatory adults aged 65 years or older with self-reported HL. Following baseline assessments, participants will be randomized to either intervention (exercise, health education, socialization and group auditory rehabilitation (GAR)) or control (GAR only) groups. The intervention group will attend a local YMCA twice a week and the control group once a week. Intervention sessions will include 45 min of strengthening, balance and resistance exercises, 30 min of group walking at a self-selected pace and 60 min of interactive health education or GAR. The control group will attend 60-min GAR sessions. GAR sessions will include education about hearing, hearing technologies, enhancing communication skills, and psychosocial support. Pre-post trial data collection and measures will include: functional fitness (gait speed, 30-s Sit to Stand Test), hearing and health-related quality of life, loneliness, depression, social participation and social support. At trial end, feasibility (recruitment, randomization, retention, acceptability) and GAR will be evaluated.

**Discussion:**

Despite evidence suggesting that HL is associated with declines in functional fitness, there are no studies aimed at addressing functional fitness declines associated with the disability of HL. This pilot trial will provide knowledge about the physical, mental and social impacts on health related to HL as a disability. This will inform the feasibility of a larger RCT and preliminary evidence about the initial effects of a novel, community-based, holistic intervention addressing both the negative psychosocial and functional physical effects of HL among older adults.

**Trial registration:**

ClinicalTrials.gov, NCT02662192. Registered on 14 January 2016

**Electronic supplementary material:**

The online version of this article (doi:10.1186/s13063-017-1792-z) contains supplementary material, which is available to authorized users.

## Background

### Conceptual framework

The World Health Organization (WHO) International Classification of Functioning, Disability and Health (ICF) [1] is a clinically relevant framework that describes disability in terms of physical impairments, activity limitations, participation restrictions and the contextual factors (environmental and personal) that interact to influence the disability (Fig. 1). The ICF provides an excellent, inclusive framework to consider the far-reaching effects of hearing loss (HL) as a disability and to evaluate the influence of interventions, such as the Walk, Talk ‘n’ Listen (WTListen) program, on participants with HL.

**Fig. 1 Fig1:**
[figure not shown]
The World Health Organization International Classification of Functioning, Disability and Health framework

Hearing loss is one of the most common chronic health problems in North America. Analysis of the audiometry data from the 2001–2008 cycles of the National Health and Nutrition Examination Surveys revealed that nearly 20% of Americans of 12 years of age or older have unilateral or bilateral HL [2]. The prevalence of HL increases with age. Audiometry results from the 2012 and 2015 Canadian Health Measures Survey [3] indicated that 78% of adults aged 60 to 79 years have audiometrically measured HL and that over 77% are undiagnosed.

The disability of HL may influence or be influenced by interactions between all domains of the ICF including personal factors (e.g., socioeconomic, education, coping mechanisms), limitations to environmental factors (e.g., relationships, supports, attitudes), body functions (e.g., declining auditory, cognitive and musculoskeletal function), limitations in activities of daily living (e.g., self-care, mobility), and participation restrictions (e.g., communication, relationships, social life). Epidemiologic studies have established independent associations between HL and poorer health-related quality of life (HRQOL: physical and mental health domains) [4, 5], social isolation [6, 7], depression [8], incident dementia [9], cognitive decline [10], increased physical dependence in activities of daily living (admission to a nursing home or requiring assistance at home) [7, 11], increased sedentary time [12], decline in functional fitness [13] including gait speed [14, 15], increased falls [16], hospitalizations [17] and a near 36% increase in age- and sex-adjusted cardiovascular and all-cause mortality (ACM) [18–21]. Applying the ICF framework to those with HL suggests that the ideal intervention aimed at addressing HL as a disability should be holistic and address personal, environmental, psychosocial and physical domains.

Provision of hearing aids (HAs) and one-on-one or group auditory rehabilitation (GAR) are currently the most common approach to treating HL. Providing HAs, education about hearing and hearing devices/technologies, psychosocial support and enhancing communication skills are the primary components of auditory rehabilitation [22]. Effective one-on-one or group auditory rehabilitation (AR) optimizes environmental and personal functioning and with the provision of HA, may address body functions (impaired auditory function) along with decreasing activity and participation limitations [23–26]; however, it does not address the well-documented declines in functional fitness (musculoskeletal: gait speed, activates of daily living (ADL) performance and increased risk for falls).

While there is some longitudinal observational evidence that two or more sessions of “muscle strengthening” exercise per week may increase longevity among adults with moderate to severe HL [27], there are no published interventions addressing the ICF domains of body function, activity and participation limitations related to declines in functional fitness in older adults with HL. Consistent with the ICF approach to HL as a disability, Chia et al. [5] emphasize the importance of understanding the synergist effects of physical disabilities, medical and social conditions on HRQOL in older adults. There is a need for more research exploring the effectiveness of strategies that not only address the ICF domains of activity and participation limitations related to impaired auditory function but that also improve functional fitness, gait speed and ADL, all of which are negatively impacted by HL.

Based on the literature and cocreated in collaboration with nearly 400 low-income seniors, Walk ‘n’ Talk for Your Life (WTL) [28] is a 10-week community-based program of socialization/health education (SHE) and graduated physical exercise program for older adults at risk of social isolation and loneliness (SI&L). While not designed for participants with HL, 30 of the first 150 WTL participants self-reported HL [29]. Compared to those without HL, participants with HL tended at baseline to be lonelier, to have a higher prevalence of possible mild depression and to have lower levels of functional fitness. By program end, both those with and without HL showed promising improvements in functional fitness and decreases in loneliness measures. In-depth, one-on-one interviews were performed with participants with self-reported HL to answer two questions: (1) Did HL affect the acceptability of WTL and if so, how? and (2) What did they feel might improve the program to address the impact (if any) of HL? From this information, (manuscript submitted) the WTListen intervention tailored for older adults with HL was developed.

In partnership with the Young Men’s Christian Association (YMCA) of Okanagan, the aim of this pilot randomized controlled trial (RCT) is two-fold: (1) to explore the feasibility and acceptability of the novel WTListen intervention for older adults with HL and (2) to provide preliminary information about the research question: In older adults with HL, what effect does a group exercise and socialization/health education intervention added to GAR have on: (a) body function impairments: (functional fitness) and activity limitations and participation restrictions (hearing-related quality of life, HRQOL) and (b) perceptions of loneliness and social network?

**Fig. 2 Fig2:**
[figure not shown]
Participant time line: Consolidated Standards of Reporting Trials (CONSORT)-style flow chart

**Fig. 3 Fig3:**
[figure not shown]
Standard Protocol Items: Recommendations for Interventional Trials (SPIRIT) figure. *Recommended content can be displayed using various schematic formats. See SPIRIT 2013 Explanation and Elaboration for examples from protocols. **List specific timepoints in this row

#### Preliminary telephone eligibility assessment

Table 1 provides the detailed inclusion and exclusion criteria. The trial coordinator, the principle investigator (PI: [name]), will verbally review the Consent Form with potential participants and answer any questions that arise.. After verbal consent is obtained, participants will be again asked, “Do you have difficulty hearing when conversing with another person in a noisy environment?” [30]. Those answering “yes” will be guided through the validated Physical Activity Readiness Questionnaire (PARQ+) [31] to confirm that they meet the inclusion criteria and are healthy enough to participate in the intervention without exacerbating any existing symptomatology [32]. Those who pass the initial PARQ+ screen and/or those who provide a physician-signed CSEP letter of “exercise readiness” and:

**Table 1 Tab1:** Inclusion and exclusion criteria of the Walk, Talk ‘n’ Listen trial

Inclusion criteria	Exclusion criteria
1. Aged 65 years or older 2. English speaking 3. Able to sign written informed consent 4. Hearing Handicap in the Elderly (HHIE-25) score of >17 [47] or a previous diagnosis of HL 5. Clearance to safely partake in the trial’s physical activities: PARQ+ (Physical Activity Readiness Questionnaire [66]) or written physician clearance for participation 6. Moderate functional fitness: gait speed >0.72 and <1.8 m/s [67] and/or 30-s STS ≥6 and <21 (within or below published sex- and age-adjusted average levels)	1. Unable to ambulate/walk for exercise 2.Serious illness limiting their ability to exercise or complete the trial 3. Contraindications to exercise: failure to fulfill the prerequisites of the PARQ+ 4. Uncontrolled hypertension (≥160/>90 mmHg) 5. Signs or symptoms of alcohol or substance dependence 6. Refusal to be randomized 7. Lack of transportation to the trial 8. Unable to commit to attending 80% or more of the sessions

*30-s STS* 30-s Sit to Stand Test, *HL* hearing loss

Self-report less than 150 min per week of physical activity [33]Have not participated in any organized exercise program for at least 6 monthsAre available and willing to attend at least 80% of the 10-week sessions in addition to completing baseline and final assessments, will be invited for final eligibility assessment

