### Measures

The primary measures: feasibility outcomes and acceptability of the pilot RCT:Recruitment strategies (how did participants hear of the trial, willingness of hearing clinics to recruit participants, number of potential participants contacting the research team and by consulting the pilot trial participants, optimal ways to reach out to isolated individuals with HL)Recruitment rates: numbers of potential participants that contact the trial center; of those, how many participated in telephone interview, how many gave verbal consent, and completed functional physical fitness testing and baseline questionnairesEligibility: how many potential participants were eligible, how many injuries, adverse events or dropouts)Randomization: acceptability/willingness to be randomized, how baseline measures compared between groupsSession adherence and overall retention rates (intervention versus control groups’ daily sign in sheets), final questionnaire completion rates and discontinuation rates (and reasons if given)Overall acceptability of the program (control versus intervention) and GAR, SHE and exercise components (participant evaluation questionnaire: Likert-style and open-ended questions)What aspects need to change? What should those changes be and how?Acceptability of student participation in the HE and GAR sessions; capacity for student trainees – benefit to research and community? Role or impact of older adult/student relationship might be something to measure in relation to loneliness…Acceptability and capacity of the YMCA to host the definitive RCTCost recovery processes for the YMCA: need to fund YMCA space, staff and time for budgeting purposes

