#### Sample size

The sample size for this pilot trial [56, 57] is based upon anticipated numbers of potential participants who contact the trial center within an 8-week recruitment period. Based on previous unpublished experience in the WTL program using pre-post data on older adults with HL, we estimate that approximately 15 per week will contact the trial center, 50–60% of those who make initial contact will meet the eligibility criteria and agree to be randomized, and at least 23 people per group at trial end to show a clinically meaningful average increase in the Sit to Stand Test (STS) of 2 [58]. This sample size will also ensure that enough data is available to generate reliable SE, SD and 95% CI on the sample size required for the large RCT with this measure as the primary outcome. A definitive RCT will be deemed feasible when at least 120 individuals contact the pilot trial center, ≥90% fulfill feasibility outcomes 2–4 and at least 70% of randomized participants fulfill outcome number 5. A larger RCT will be deemed acceptable if at least 85% of participants find the GAR, exercise and SHE sessions highly acceptable or acceptable.

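### Refusing randomization is an exclusion, yet willingness to be randomized is judged against a 90% go bar with no denominator: among eligible people it cannot fail, and among all contacts the plan already expects to miss it

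*Protocol article*

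**What the plan says.** Four places in the protocol article bear on this.

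- **Table 1 (Preliminary telephone eligibility assessment).** Exclusions include "6. Refusal to be randomized 7. Lack of transportation to the trial" and "8. Unable to commit to attending 80% or more of the sessions". The telephone screen repeats the 80% attendance condition.
- **Measures, primary feasibility outcomes.** The fourth item in the list is willingness to accept randomization, together with a comparison of baseline measures between groups. The fifth is session adherence, retention, questionnaire completion and discontinuation. The third asks "how many potential participants were eligible, how many injuries, adverse events or dropouts".
- **Sample size, go rule.** "A definitive RCT will be deemed feasible when at least 120 individuals contact the pilot trial center", and in addition "≥90% fulfill feasibility outcomes 2–4 and at least 70% of randomized participants fulfill outcome number 5". The 70% part names its denominator (randomized participants). The 90% part names none.
- **Sample size, planning figures.** "we estimate that approximately 15 per week will contact the trial center" "within an 8-week recruitment period", and "50–60% of those who make initial contact will meet the eligibility criteria and agree to be randomized".

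The list numbering was lost when the text was extracted, so the fourth and fifth items are matched to outcomes 4 and 5 by their order.

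**The concern.** One behaviour, declining to be randomized, has two roles. It makes a person ineligible, and it is also what feasibility outcome 4 is meant to measure. Whether a refuser counts against the 90% bar therefore depends on how the screening log codes that person and on which denominator is used. The article settles neither.

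The pilot's main product is a decision on whether a definitive trial is feasible. An item of the go rule that is satisfied by definition tells the planners of the larger trial nothing about acceptance of randomization. An item that fails when recruitment goes exactly as planned is no more useful. The limitations in the Discussion name reluctance to be allocated to a control group as a known reason for declining, so this is a foreseeable barrier that the pilot ought to be able to measure.

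**Working it through.** **Inputs.** 15 contacts per week, 8 weeks, 50–60% eligible and agreeing, and the 90% and 70% bars (all from Sample size); 60 to be randomized (Trial design). The documents give no number expected to be excluded under criteria 6, 7 or 8, so the refuser counts below are illustrative.

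**The plan's own figure.** Contacts: 15 × 8 = 120, which equals the contact threshold in the go rule. Randomized: 120 × 0.50 = 60 to 120 × 0.60 = 72. The planned 60 is reproduced at the lower end.

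**Willingness under three denominators.** Let N be the number randomized and r the number of otherwise-eligible people who refuse.

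1. *Eligible under Table 1.* Refusers are excluded, so willingness = N/N = 60/60 = 100% whatever r is.
2. *All contacts.* The planned share is 60/120 = 50% to 72/120 = 60%. Reaching 90% would need 0.90 × 120 = 108 people, against 60 to 72 expected.
3. *Everyone who meets all other criteria.* Willingness = N/(N + r). The bar is met when N/(N + r) ≥ 0.90, that is, when r ≤ N/9.
   - N = 60: 60/9 = 6.7, so at most 6 refusers. 60/66 = 90.9% passes; 60/67 = 89.6% fails; with 12 refusers, 60/72 = 83.3%.
   - N = 72: 72/9 = 8, so at most 8 refusers. 72/80 = 90.0% passes; 72/81 = 88.9% fails.

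Only the third denominator lets the observed refusals decide the result.

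**Adherence (outcome 5).** The bar is 0.70 × 60 = 42 participants. Treating each participant as fulfilling the outcome independently with true probability p, the binomial chance of at least 42 of 60 is:

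| True rate p | P(at least 42 of 60) |
|---|---|
| 65% | 0.25 |
| 70% | 0.56 |
| 75% | 0.85 |
| 80% | 0.98 |

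Screening on stated commitment may raise p, but it does not guarantee a pass.

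**The case against.** The strongest reply is that the article never says refusers leave the denominator. The planning sentence treats eligibility and agreement as separate steps, and the Discussion lists unwillingness to be randomized among reasons for declining, not as ineligibility. Counts at each screening stage are planned, and reasons for declining will be sought. A condensed article may also leave log coding and denominators to the full protocol or analysis plan.

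Much of this stands. A flat statement that the bar cannot fail would go beyond the text, because it is true only for the Table 1 denominator. The 90% rule also covers outcomes 2 and 3, so the rule as a whole can fail even when the willingness item is saturated. The 50–60% figure pools every reason for not entering and is not a refusal rate.

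What does not stand is the defence that this is only missing detail. The exclusion and the go rule are both printed in the article, and neither the Table 1-eligible nor the all-contacts reading yields an informative test. Collecting counts and reasons does not help if the decision rule does not use them.

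A reader might also infer that criteria 7 and 8 make the 70% adherence threshold pass by construction. The documents do not support that. Those criteria screen on transport and stated commitment before entry, while outcome 5 is observed adherence and retention in randomized participants. That is enrichment, and it would carry over to a definitive trial with the same entry rules. Transport has no threshold of its own.

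**Conclusion.** The point holds for criterion 6 and the willingness item of outcome 4. With the denominator unstated, the item is either fixed at 100% (people eligible under Table 1) or expected to reach only 50–60% against a bar of 90% (all contacts). With refusers counted among otherwise-eligible people, the decision turns on very few of them: the seventh refuser per 60 randomized, or the ninth per 72.

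The conclusion assumes that list order gives the outcome numbers and that no document outside the article already defines the denominator. How far the stated willingness would be inflated cannot be computed, because no refusal count is given. For outcome 5 the effect is limited to a more favourable starting population.

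**What to change.** - Keep criterion 6 as a condition of enrolment, but log refusal of randomization as its own category, separate from ineligibility for other reasons.
- State in the go rule that the 90% willingness bar applies to everyone who meets all other criteria, with refusers in the denominator: randomized / (randomized + otherwise-eligible refusers).
- Beside the outcome 5 result, report how many people were screened out under criteria 7 and 8, by reason. The 70% threshold itself need not change on this account.

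The cost is one coding rule in the screening log and one sentence in the plan, since the stage counts are already to be collected. People need not give reasons for declining, so a category for unknown reason is needed. The downside is that the stated willingness figure may be less favourable, and the go rule may fail where the Table 1 denominator would have let it pass.

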#### Final eligibility assessment

Final eligibility assessment (functional fitness testing) and baseline questionnaire completion will take place at the trial site (a local YMCA site) and be performed by members of the trained research team after signed informed consent has been obtained.

### Intervention

The trial will occur at different times on the same days for the intervention and the control groups. The intervention groups (GAR-SHE-exercise) will visit the YMCA twice a week (2 days apart) for 10 weeks. On the first visit each week they will attend a 1-h interactive GAR session (details of the session will be the same as for the control groups) and 90 min of exercise and walking. On their second visit each week they will attend a 1-h interactive SHE session followed by 90 min of exercise and walking. The exercise intervention will be offered to the control group after the RCT is completed (weeks 13–24). Control groups (GAR only) will attend a 1-h interactive GAR session at the YMCA once a week for 10 weeks. Trained students will help the PI to facilitate the GAR and SHE sessions. GAR sessions will be held in the same small, carpeted room and exercise sessions will occur in a small gym facilitated by a fitness instructor using a microphone and FM amplification system.

#### GAR sessions

GAR sessions (control and intervention groups) will be guided by a modification of the GROUP program [36] (http://idainstitute.com/toolbox/group/). The GROUP program is an IDA Institute-sponsored, web-based, interactive video-enabled program that provides a step-by-step guide for implementing and facilitating GAR programs. The guide provides instructions and informational content/handouts of best practices informed by leading GAR experts along with ethnographic videos allowing facilitators to see GAR in action. In addition, an audiologist ([name]) will facilitate the GAR session on HAs and hearing assistive technology for all groups. GAR sessions will include ice-breaking activities, ground rules for participants, goal setting, multiple communication strategies, coping with HL, handling difficult listening situations, types and uses of hearing assistive technologies, local resources and “advocating for yourself and others with HL.” Psychosocial, mindfulness and stress-reduction strategies will also be included. Participants will engage in practical exercises to do as a group and at home. They will be encouraged to review their GAR handouts with their communication partners (CPs: spouse, significant other or friend). In addition to the weekly sessions, a single 3-h session will be scheduled to include participants’ CPs. In this session, participants and their communication partners will discuss their own communication challenges and together decide upon and practice relevant communication strategies.

